#### Extension flexion plain radiograph

Dynamic flexion-extension radiographs are used to assess the functional stability – the healing – of a type-2 odontoid fracture [34]. Instability is defined by a > 3.5-mm listhesis and/or a relative angulation of > 11° [35].

#### Dual energy X-ray absorptiometry

Osteoporosis will be evaluated with DXA of the hip and lumbar spine [36].

#### Other tests

Blood samples (including haemoglobin, electrolytes)Socio-demographics, living situation (1. home, 2. nursing home, 3. hospital)Charlson Comorbidity Index [37, 38]VAS for pain (0 to 100)

### Data collection, management and analysis

#### Data collection and management

The USOFT baseline data are recorded in a paper-based clinical record folder. Prior to inclusion, the data from each patient are collected by a spinal surgeon or a dedicated study nurse. All physician-reported outcome measurements are recorded during and after the evaluation in the folder. Patient-reported outcome measurements are recorded in the Clinical Trials extension of the Swedish Spine Registry (SweSpine) [39]. Any protocol deviations are recorded either in the case file or in the medical records; a clinical study nurse ensures that all protocol deviations and adverse events are recorded in the database.

Every allocated subject will be coded with a specific patient number. The study data will be transferred to a pre-made computer-based table (Microsoft Excel, V.15.32, Microsoft, Redmond, WA, USA) and the Clinical Trials extension of SweSpine [39]. The completed files will be stored securely in the clinical research unit for the next 15 years.

#### Access to data

Data safety, data quality and statistical analysis will be managed by the principal investigator who is responsible for notifying any issues that may arise during the USOFT. Data are collected and stored according to Good Clinical Practice guidelines and are available to all participating study sites. Any data safety issue occurring during the clinical trial will be reported to the principal investigator.

### Statistics

For statistical analysis, R version 3.4.1 (R Foundation for Statistical Computing, Vienna, Austria) will be used. The results will be presented according to the CONSORT Statement for non-pharmacological interventions [26]. The analysis will be performed by intention-to-treat (ITT), and sensitivity analyses will include a per-protocol analysis.

Missing values will be imputed using multiple imputation by use of chained equations as implemented in the R package “mice” with 20 iterations [40]. Details of the statistical analysis are listed in Table 1.

**Table 1 Tab1:** Variables, measures and methods of analysis

Variable/Outcomes	Hypothesis	Outcome measures	Methods of analysis
*Baseline data:*	There is no difference between the two groups	Gender, age, Katz ADL, CCI, nursing home/hospitalisation, smoking status	Absolute numbers, percentages for categorical variables and the minimum, maximum, mean, SD and quartiles for quantitative variables
*Primary:*			
Function	There is a clinically important difference between the two groups, with improvement comparing baseline data with data from 6 weeks, 12 weeks, and 1 year. Surgical treatment is hypothesised to be superior	NDI (0–100%) [continuous]	Student *t* test, chi-square, Mann-Whitney, Fisher’s exact test. Time-dependent differences between AUC
*Secondary:*			
Health-related quality of life	There is a clinically important difference between the two groups	EQ-5D [continuous]	Student *t* test, chi-square, Mann-Whitney, Fisher’s exact test Time-dependent differences between AUC
Pain	There is a clinically important difference between the two groups	VAS (0–100) [continuous]	Students *t* test, chi-square, Mann-Whitney, Fisher exact test Time-dependent differences between AUC
Non-union	The non-union rate is lower in the surgical group	Bone bridge in CT [binary], mobility on extension-flexion radiographs [binary],	Chi-square test
Mortality	The survival is greater in the surgical group	all-cause mortality [binary], time to death [continuous, censored]	Kaplan-Meier analysis, Cox regression models, additional subdistribution hazards approach
Osteoporosis	There is no difference between the two groups	The bone density is > 2.5 standard deviations below normal DXA T-score [binary]	Chi-square
*Subgroup analysis:*			
septuagenarians vs. octogenarians vs. nonagenarians	Treatment effect is diminished in nonagenarians		
Goel-Harms technique vs. Magerl technique	There is no difference between the two groups		
Male vs. female	There is no difference between the two groups		
*Sensitivity analysis:*			
Per-protocol analysis		All outcomes	Students *t* test, chi-square, Mann-Whitney, Fisher exact test
Adjusting for baseline covariates	All outcomes		Uni-and multivariate adjusted logistic regression and Cox proportional hazard models
Adjusting for mortality	All outcomes		subdistribution hazards approach

*CT* computed tomography*, NDI* Neck Disability Index, *EQ-5D* EuroQol, *VAS* Visual Analogue Scale, *CCI* Charlson Comorbidity Index, *Katz ADL* Activities of Daily Living score according to Katz, *DXA* double x-ray absorptiometry, *AUC* area under the curve

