### Study outcome measures

#### Primary outcome measure

The primary outcome variable is the difference in the Neck Disability Index (NDI) at baseline and 1 year after injury [24, 25]. Both comparing differences within the groups (baseline vs. NDI at 1 year), but also differences between the groups. The same evaluation will be made at 6 weeks and 3 months.

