### Limitations

This randomised controlled study employs an open-label design, where both the investigator and the patient know which treatment they will receive. Unfortunately, the open-label design has an inherent selection bias, where patients can drop out during enrolment or give informed consent prior to inclusion in this study.

A review of the allocation concealment methods of major medical journals in 2015 found that 19% of trials involved an inadequate allocation method and 22% were without appropriate reporting of the randomisation method [44]. Our protocol uses SNOSE allocation concealment and simple randomisation. The sealed envelope technique requires good clinical practice and discipline of the part of the enrolling physician, since translucency and premature opening can corrupt the randomisation process [45]. Simple randomisation avoids deciphering block randomisation but risks different sample sizes in treatment and control groups. Transparency of the randomisation process and close supervision of the randomisation process by the principle investigator and the R&D Council will control the quality of this RCT.

One-year progression-free survival and 1-year all-cause mortality are common primary endpoints for RCTs. Due to the frailty of the elderly study participants, an overlap of an unrelated and natural cause of death with injury-related mortality causes high variation and would require a significantly greater sample size. Since HRQoL defines the value of life years gained, this study uses the NDI as the primary endpoint, with EQ-5D and survival as secondary endpoints.

We have planned to deal with dropouts for death in our sample size calculation, adopting an inflation rate. However, death will represent an important competing event. It is possible that if surgery has a favourable impact on mortality, more people will die in the control group, and earlier. These people who die might be those more compromised. This means that people in the control group who survive at 1 year might be those who are healthier, which might dilute the actual effect of the intervention on disability. To adjust for competing events we aim to use a subdistribution hazards approach to adjust for mortality [46].

The results from this study will provide overdue evidence regarding the treatment of type-2 odontoid fractures in the elderly. The QALYs gained with optimal treatment will support policy-makers and clinicians with their informed decisions.

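### The only mortality adjustment named for the NDI, a subdistribution hazards model, cannot be fitted to a continuous score, and the imputation rule makes no exception for patients who have died

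*Protocol article*

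**What the plan says.** The protocol article addresses death in four places.

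- **Methods, Statistics.** "The analysis will be performed by intention-to-treat (ITT), and sensitivity analyses will include a per-protocol analysis". Then: "Missing values will be imputed using multiple imputation by use of chained equations". Death is not mentioned, and the reader is sent to Table 1 for details.
- **Table 1.** The primary outcome is listed as a continuous NDI percentage. Its methods are the t test, chi-square, Mann-Whitney, Fisher's exact test and differences in area under the curve. Among the sensitivity analyses, the row on adjusting for mortality covers all outcomes and names one method, the "subdistribution hazards approach". The same approach is listed as an addition for mortality itself, which is all-cause.
- **Methods, Sample size.** 16 patients per group are needed, and eight more per group are added for 29% mortality at 1 year, giving a minimum of 24.
- **Discussion, Limitations.** "We have planned to deal with dropouts for death in our sample size calculation, adopting an inflation rate". The authors then concede that this does not settle the matter: "However, death will represent an important competing event". After explaining that healthier survivors in the control group could dilute the effect on disability, the text gives its remedy: "To adjust for competing events we aim to use a subdistribution hazards approach to adjust for mortality".

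The Primary outcome measure section defines the endpoint as a score: "The primary outcome variable is the difference in the Neck Disability Index (NDI) at baseline and 1 year after injury".

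**The concern.** Death is probably the largest single reason why a 1-year NDI will be absent. The protocol recognises this and names a remedy, but the remedy does not suit the type of outcome. A subdistribution hazards model describes the time to one type of event when another can prevent it. It gives no comparison of mean or ranked scores at a fixed visit.

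Two parts of the plan also imply different populations. The sample size assumes that patients who die leave the analysis. The imputation rule, taken at its word, puts a value back for each of them. The first describes disability among people alive at 1 year. The second describes a disability score for people who have none. If the choice is left open, it can be made after the results are known, in a trial where treatment is not masked.

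**Working it through.** **1. The plan's own figure.** Inputs from Sample size: difference 3.5, SD 3.5, two-sided 0.05, power 80%, mortality 29%.

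- Normal approximation: n = 2 × (1.960 + 0.842)² × (3.5/3.5)² = 15.7, so 16 per group, as stated. The t-test version gives 16.7, so 17.
- Inflation: 16/0.71 = 22.5, so 23; 17/0.71 = 23.9, so 24. The stated 24 is reproduced.

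The arithmetic is sound. It also shows the intent: dividing by the surviving fraction makes sense only if the dead contribute no NDI.

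**2. How many patients are affected.**

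- 29% in both arms: 50 × 0.29 = 14.5 deaths, or 7.25 per arm of 25.
- 29% without surgery, and the hazard ratio of 0.64 quoted in the Evidence section applied to surgery: 1 − 0.71^0.64 = 0.197. Deaths are 25 × 0.29 + 25 × 0.197 = 7.25 + 4.92 = 12.2.

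The range is therefore about 12 to 14.5 of 50. The hazard ratio comes from patients aged 65 and over. The same section says the advantage seems to diminish at 80 and over, so the lower figure is only an illustration for a trial of patients aged 75 and over.

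**3. What the choice of population changes.** For a 3.5-point difference and t-test power:

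- Survivors only: 25 × 0.71 = 17.75 per arm, power 0.82.
- Every randomised patient counted as having a value: 25 per arm, nominal power 0.93.

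The second figure treats imputed values as observed, so it shows apparent rather than real information.

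**4. Does the named model fit each outcome?**

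| Outcome | Type in Table 1 | Subdistribution hazards |
|---|---|---|
| NDI | continuous | no event or threshold defined; cannot be fitted |
| EQ-5D | continuous | same |
| VAS pain | continuous | same |
| All-cause mortality | binary; censored time to death | no competing event; reduces to an ordinary survival model |

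**5. Size of the survivors-only bias.** Assumptions not in the documents: frailty is normal; the frailest die; frailty correlates ρ with NDI; surgery has no true effect on NDI; SD 3.5; mortality 29% versus 19.7%. The survivors' mean shifts by −ρ × 3.5 × φ(c)/(1 − m), where c is the normal quantile at 1 − m.

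- m = 0.29: c = 0.553, and φ(c)/(1 − m) = 0.342/0.71 = 0.482.
- m = 0.197: c = 0.853, and φ(c)/(1 − m) = 0.277/0.803 = 0.345.
- Difference between arms: ρ × 3.5 × (0.482 − 0.345) = 0.14, 0.24 and 0.33 points for ρ = 0.3, 0.5 and 0.7. Simulation gives the same values.
- If frailty predicts death less sharply (loading 0.7), simulation gives 0.10, 0.16 and 0.24.

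The shift is against surgery, which is the dilution the Limitations section describes. At 0.10 to 0.33 points it is 3% to 9% of the 3.5-point MCID. With equal mortality in the two arms it would be zero under this model.

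**The case against.** The strongest reply is that the plan never says it will impute for the dead. It speaks of missing values, and a score after death need not count as one. The Sample size and Limitations sections suggest that deaths were expected to leave the NDI analysis, and who enters an imputation model is commonly settled in an analysis plan that is not shown here. This stands in part. A reader might infer that the plan prescribes invented scores for patients who have died. The text does not go that far; it is silent, and only its literal scope under intention to treat includes them.

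A second reply is that the mortality row is a sensitivity analysis in a table of method menus, to be read as applying where suitable. That would help if the row stood alone. But the Limitations section offers the same method as the answer to dilution of the disability effect, which is exactly where it cannot be used. An unseen analysis plan would have to depart from both places to supply a usable adjustment.

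A third is that competing causes of death exist, since the Limitations section separates injury-related from unrelated death. But Table 1 names all-cause mortality and defines no cause-specific outcome, so nothing competes there. Listing the method for that outcome is redundant rather than harmful.

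**Conclusion.** The point holds as an error of method and an inconsistency. The one analytic adjustment for death that is named for the primary endpoint cannot be carried out. The imputation rule, read literally, also conflicts with a sample size that removes the dead. About 12 to 14.5 of 50 one-year values depend on how this is settled. The lower end rests on a hazard ratio from a younger population.

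The sample size itself is not at fault, and no large bias has been shown. The 0.1 to 0.3 points for a survivors-only comparison rest on assumed frailty correlations and on mortality differing between arms.

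Two stronger conclusions might be inferred. One is that a survival benefit of surgery would be erased or reversed in the score analyses. No calculation supports a reversal, and mortality is analysed separately by Kaplan-Meier and Cox methods. The other is that a definite QALY error per arm can be stated. The documents give neither a QALY formula nor a utility for these patients, and the timing of deaths within the year is unknown, so no such figure is justified.

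**What to change.** 1. In Statistics, restrict multiple imputation to patients alive at the visit concerned.
2. State that the primary NDI comparison is made in patients alive at 1 year. This matches the sample size and keeps the survivor-selection limitation that the Discussion already discloses.
3. In Table 1 and Limitations, replace the subdistribution hazards approach for NDI, EQ-5D and VAS with a sensitivity analysis of all randomised patients, in which death ranks below the worst score and the groups are compared by Mann-Whitney, a test already listed.
4. Drop subdistribution hazards for all-cause death. Keep it only for a time-to-event outcome for which death truly competes, should one be defined.
5. In any QALY calculation, count utility as zero from death onward.

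The cost is revised wording and one extra analysis, with no new data and no change to patient care. The downside is that the worst-rank result mixes death with disability, so it must be read beside the survivors' result.

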**Methods:**

The Uppsala Study on Odontoid Fracture Treatment (USOFT) is a multicentre, open-label, randomised controlled superiority trial evaluating the clinical superiority of the surgical treatment of type-2 odontoid fractures, with a 1-year Neck Disability Index (NDI) as the primary endpoint. Fifty consecutive patients aged ≥ 75 years, with displaced type-2 odontoid fracture, are randomised to non-surgical or surgical treatment. Excluded are patients with an American Society of Anaesthesiologists (ASA) score ≥ 4, dementia nursing care or anatomical cervical anomalies.

The minimal clinically important difference of the NDI is 3.5 points. A minimum of 16 patients are needed in each group to test the superiority with 80% power. By considering a 1-year mortality forecast of 29%, up to 25 participants are recruited in each group.

The non-surgical group is fitted with a rigid cervical collar for 12 weeks. The surgical group is treated with a posterior C1–C2 fusion. All participants are monitored with regard to the NDI, EuroQol score (EQ-5D), socio-demographics and computed tomography (CT) at the time of injury, at 6 weeks, 3 months and 12 months. At 12 months, a dynamic radiographical investigation of upper cervical stability is performed.

The secondary endpoints are: EQ-5D score, activities of daily living (ADL), bony union, upper cervical stability and mortality.

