**Fig. 2 Fig2:**
[figure not shown]
Participant timeline. *CT* computed tomography, *CCI* charlson comorbidity index, *EQ-5D* euroQol, *NDI* neck disability index, katz *ADL* activities in daily life according to katz, *DXA* double x-ray absorptiometry

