### VAS

The VAS will be evaluated using the *t* test, the Mann-Whitney *U* test or Fisher’s exact test.

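### Table 1 lists an AUC comparison for pain VAS, but the stated VAS schedule has only two time points, so that AUC carries no time course

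*Protocol article*

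**What the plan says.** Four places in the protocol article bear on this.

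- **Statistics, Table 1, Pain row.** The outcome is VAS (0–100), marked continuous. The methods cell lists a t test, chi-square and Mann-Whitney, and ends "Fisher exact test Time-dependent differences between AUC". The rows for NDI and EQ-5D carry the same AUC entry, "Time-dependent differences between AUC". The table footnote expands AUC only as "area under the curve".
- **Secondary outcome measures.** The VAS is listed with two times, baseline and one year. The Other tests section identifies the scale: "VAS for pain (0 to 100").
- **Visit schedule.** The Abstract states what is followed at injury, 6 weeks, 3 months and 12 months: "All participants are monitored with regard to the NDI, EuroQol score (EQ-5D), socio-demographics and computed tomography (CT"). Pain VAS is not named. For the NDI, the Primary outcome measure section adds: "The same evaluation will be made at 6 weeks and 3 months". No such sentence exists for the VAS.
- **VAS analysis section.** "The VAS will be evaluated using the" t test, the Mann-Whitney U test or Fisher's exact test. No AUC is mentioned.

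**The concern.** An area under the curve is used to summarise a course over several visits. The NDI and EQ-5D have four visits, so the entry makes sense in their rows. The Pain row has the same entry without the repeated measurements behind it. On the stated schedule there is no pain value from the 12-week collar period or from recovery after surgery, which is where a time-dependent difference between the arms would be expected to show.

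Two things are at stake. First, the table promises information on time course that the planned data cannot supply. Second, the row does not say which of its methods is the principal one. If the AUC were chosen, the comparison would mix the one-year value with a baseline value that the treatment cannot have affected.

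**Working it through.** **The plan's own figures.** The article gives no effect size, SD or power for the VAS, so there is no pain figure to reproduce. Its sample size (16 per group from a 3.5-point difference and SD 3.5, 80% power, two-sided 0.05) concerns the NDI. It reproduces as 2(1.96+0.84)² = 15.7, rounded up to 16, and has no bearing here.

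**Step 1: what a two-point AUC is.** Let b be the baseline and y the one-year VAS, with AUC expressed per unit of follow-up time.

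- Uncorrected trapezoid: (b + y)/2.
- Baseline-subtracted trapezoid: (0 + (y − b))/2 = (y − b)/2.

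Neither contains anything beyond b and y.

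**Step 2: what it cannot see.** Take two hypothetical patients who both go from 70 to 20, with values invented for weeks 6 and 12.

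- Early relief (70, 30, 25, 20 at weeks 0, 6, 12, 52): (6×50 + 6×27.5 + 40×22.5)/52 = 1365/52 = 26.3.
- Late relief (70, 65, 55, 20): (6×67.5 + 6×60 + 40×37.5)/52 = 2265/52 = 43.6.

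On the two-point schedule both score (70+20)/2 = 45 uncorrected, or (20−70)/2 = −25 baseline-subtracted. A patient going from 50 to 40 also scores 45 uncorrected.

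**Step 3: efficiency against the one-year VAS.** Assume equal SD s at both times, correlation r, no expected baseline difference between randomised arms, and a one-year difference d.

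- Uncorrected: effect d/2, variance s²(1+r)/2. Variance factor relative to the one-year VAS: 2(1+r).
- Baseline-subtracted: effect d/2, variance s²(1−r)/2. Factor: 2(1−r).
- One-year VAS adjusted for baseline: effect d, residual variance s²(1−r²). Factor: 1−r².

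The document gives no r, so a range is shown. A factor above 1 means more patients are needed than for the unadjusted one-year comparison.

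| r (assumed) | AUC, uncorrected | AUC, baseline-subtracted | One-year VAS, baseline-adjusted |
|---|---|---|---|
| 0 | 2.0 | 2.0 | 1.00 |
| 0.3 | 2.6 | 1.4 | 0.91 |
| 0.5 | 3.0 | 1.0 | 0.75 |
| 0.7 | 3.4 | 0.6 | 0.51 |

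The adjusted comparison is never worse than either AUC, because 1−r² = (1−r)(1+r) and neither bracket exceeds 2.

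**The case against.** The best case for the plan is that little depends on this entry. The AUC comes last in a list of methods, the VAS analysis section leaves it out, and a valid one-year comparison between the arms is available as the plan stands. The outcome is secondary; the primary endpoint, the sample size and the interim rule do not depend on it. All of that stands, and it limits the weight of the point.

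The missing figure also needs care. Follow-up is said to accord with Fig. 2, captioned "Participant timeline", which is not shown in the text at hand. It could list VAS at the interim visits, and an outcome list may name comparison times rather than every collection time. The caption's abbreviations include EQ-5D, NDI and Katz ADL but not VAS, which suggests otherwise without settling it. If the figure does list interim VAS, it disagrees with the outcome section and the passages still need reconciling. The EQ VAS does not rescue the entry: it belongs to the EQ-5D and rates self-assessed health, whereas the row is labelled Pain.

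Three stronger readings are tempting, and the document does not support them.

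- A reader might infer that the AUC cannot be computed. It can, as Step 1 shows; it just says nothing about time course.
- A reader might infer that the pain analysis needs two to three times the patients. That holds only for an uncorrected trapezoid, for r between 0 and 0.5, and only if the AUC displaces the one-year test. The article does not define the AUC, and it frames its primary outcome as change from baseline, so the baseline-subtracted form is equally plausible. In that form nothing is lost at r = 0.5.
- A reader might infer that the result will be presented as pain burden over the year. No section says so.

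**Conclusion.** The inconsistency is real and minor. On the stated two-point schedule, the AUC in the Pain row adds nothing to the baseline and one-year values, under either definition and whatever r is. The VAS analysis section does not support the entry either.

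No single figure can be given for lost efficiency. It ranges from a factor of 3.4 to a gain (0.6) over the definitions and correlations tabulated, assumes equal SDs, and is relevant only if the AUC is used in place of the one-year comparison. The conclusion on time course rests on the VAS timing in the Secondary outcome measures section being complete, which the unseen Fig. 2 could contradict.

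**What to change.** 1. Delete the AUC from the Pain row of Table 1. Leave it for the NDI and EQ-5D, which have the visits to support it.
2. Name one principal pain analysis: the between-arm difference in one-year VAS from a linear model with baseline VAS as covariate (ANCOVA), under the intention-to-treat and multiple-imputation approach already stated. Table 1 does list baseline adjustment for all outcomes as a sensitivity analysis, but the models named there are logistic and Cox, which do not suit a continuous VAS.
3. Make Table 1, the Secondary outcome measures section and the VAS analysis section agree, and check them against Fig. 2.

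The cost is one table cell, one sentence and one regression on data already planned, handled as a protocol modification under the article's own amendment procedure. The adjustment uses one degree of freedom and gains nothing if r is near zero.

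Adding VAS at the interim visits to keep the AUC is not worthwhile. Inclusion began in February 2012 and was due to end before 31 December 2018, so most patients would already be past those visits. Restricting an AUC to those with interim values would be a complete-case analysis at odds with the stated intention-to-treat and imputation plan.

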#### Non-surgical treatment

The patient will be provided with a well-fitted and rigid collar, such as the Philadelphia collar (Ossur, Sollentuna, Sweden) or the Aspen collar (Aspen Medical Collars, Irvine, CA, USA). The collar will be worn 24 h a day for 12 weeks. The collar may be removed for short periods of time for personal hygiene when the patient is supine in bed.

CT scans will be repeated after 1 week, 6 weeks and 3 months. In case of increasing fracture displacement, or symptomatic non-union, the fracture will be treated surgically with a posterior C1–C2 fusion. The crossover will be documented, but all data will be analysed according to the intention-to-treat (ITT) principle.

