#### Surgical treatment

The patient will be surgically treated with an instrumented posterior C1–C2 fusion, including an autologous iliac crest bone graft. The primary fixation technique involves transarticular C1–C2 screws, according to Magerl, and the C1 claw device [20]. In case of anatomical aberrations or a concomitant C1 arch fracture, other techniques may be used: e.g., C1 screws, according to Goel-Harms [21, 22], or translaminar C2 screws, according to Wright [23].

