#### Analysis of the primary outcome

Multiple regression analysis of subgroup factors will allow for the determination of important factors affecting the NDI. The differences will be considered statistically significant if the *p* value is less than 0.05.

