#### Subgroup analysis

We will perform a separate analysis of participant socio-demographics, type-2 odontoid fracture subgroup, the specific type of surgery (categorical: Magerl-Atlas claw or Goel-Harms) and osteoporosis status (DXA score).

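### Fusion technique is chosen after randomisation, by anatomy or C1 arch fracture, yet is listed as a subgroup with a no-difference hypothesis and falls within the NDI regression

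*Protocol article*

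**What the plan says.** Fusion technique appears in three places as a subgroup factor. It is in the list under Study outcome measures, Subgroup analysis. The later Subgroup analysis section promises a separate analysis of "the specific type of surgery (categorical: Magerl-Atlas claw or Goel-Harms". Table 1 (Statistics) has the row "Goel-Harms technique vs. Magerl technique" with the hypothesis "There is no difference between the two groups"; its outcome and method cells are empty and no margin is given.

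The section Analysis of the primary outcome adds: "Multiple regression analysis of subgroup factors will allow for the determination of important factors affecting the NDI". It sets significance at p below 0.05 and does not say which of the listed factors are meant.

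The section Surgical treatment describes how technique is decided. The default is stated as "The primary fixation technique involves transarticular C1–C2 screws, according to Magerl, and the C1 claw device". The exception reads "In case of anatomical aberrations or a concomitant C1 arch fracture, other techniques may be used", and the examples include "translaminar C2 screws, according to Wright", which has no level in the two-category factor. In the comparator arm, "The patient will be provided with a well-fitted and rigid collar", so these patients have no fusion technique unless they cross over to a posterior C1–C2 fusion, which the section Non-surgical treatment allows.

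No passage restricts the technique comparison to operated patients, calls it descriptive, or mentions confounding by the reason for the choice. The Limitations section is silent on it.

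**The concern.** A subgroup of a randomised comparison is defined by something known at randomisation and present in both arms, so that treatment can be compared with control within each level. Age, sex, ASA class and Grauer type meet that test. Fusion technique does not: there is no control group within a technique level.

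What can be estimated is Magerl against Goel-Harms among operated patients. The article's own rule sends patients with aberrant anatomy or a C1 arch fracture away from the default, so the two groups differ by design in features that may bear on NDI. Case mix could then be reported as an effect of technique.

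Two further consequences follow. If technique enters a two-arm regression, it is tied to treatment. And a no-difference hypothesis with no margin, in a group this small, invites a non-significant result to be taken as support.

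**Working it through.** **1. The plan's own figure.** Sample size gives a difference of 3.5 points, SD 3.5, two-sided 0.05 and 80% power. The normal formula gives n per arm = 2 × (1.96 + 0.84)² × (3.5/3.5)² = 15.7, rounded up to 16. This matches the stated 16. (The exact t test gives 78.1% power at 16 and needs 17.) Inflating for 29% mortality gives 16/0.71 = 22.5, so 23, or 24 if one starts from 17; the article states a minimum of 24, and up to 25 per group in the Abstract.

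**2. Patients available for the technique contrast.** The number evaluable at 1 year is 25 × 0.71 = 17.75, about 18. The 29% is stated for non-surgical treatment; using it for the surgical arm is an assumption.

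**3. Precision.** The split between techniques is not given, so it is assumed and shown as a range. Because one technique is the default, uneven splits are the more likely ones. With SE = 3.5 × √(1/n₁ + 1/n₂), half-width = t(0.975, 16) × SE = 2.12 × SE, and power from the noncentral t with noncentrality 3.5/SE:

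| Split | SE | Noncentrality | Power for 3.5 points | 95% CI half-width |
|---|---|---|---|---|
| 15:3 | 2.21 | 1.58 | 32% | 4.7 |
| 14:4 | 1.98 | 1.76 | 38% | 4.2 |
| 12:6 | 1.75 | 2.00 | 47% | 3.7 |
| 9:9 | 1.65 | 2.12 | 51% | 3.5 |

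A non-significant result means only that the estimate is smaller than the half-width. In every row, the interval around a non-zero, non-significant estimate reaches about 3.5 points or beyond, so the trial's own MCID is not excluded.

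**4. Sensitivity to the number evaluable.**
- With 17 (24 × 0.71), power is 24% at 15:2 and 49% at 9:8.
- If surgical mortality were lower, for example by the hazard ratio of 0.64 quoted in the Evidence section, survival would be 0.71^0.64 = 0.80 and about 20 of 25 would be evaluable. The most favourable split, 10:10, gives a half-width of 3.3.
- With all 25 evaluable, power runs from 26% (23:2) to 67% (13:12). At 13:12 the half-width is 2.9, so the estimate would have to lie within 3.5 − 2.9 = 0.6 points of zero to exclude the MCID. Non-significance alone would still not do it.

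**5. The regression.** Ignore crossovers, let S = 1 for surgery and G = 1 for Goel-Harms, and set G to 0 for collar patients. In mean NDI = b₀ + b₁S + b₂G, b₁ is Magerl minus collar. The randomised contrast is b₁ + p·b₂, where p is the share of Goel-Harms in the surgical arm. The two differ by p·b₂. As an illustration, if the technique groups differed by 3.5 points for any reason, case mix included, the gap would be 3/18 × 3.5 = 0.6 points at 15:3 and 9/18 × 3.5 = 1.75 points at 9:9.

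The other codings do no better:
- Dropping patients without a technique removes the collar-only patients.
- Collar as a third level beside a treatment term is collinear.
- A three-level factor in place of treatment can be fitted, but no single coefficient is then the randomised contrast, and the technique contrast stays confounded.

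**The case against.** The strongest reply is that this is one exploratory row in a condensed article, and that the primary comparison does not depend on it. Much of that stands.

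- A reader might infer that the primary result is corrupted. The text does not support this. The between-arm NDI comparison is the Function row of Table 1, which technique does not enter. The regression is described as a search for factors affecting the NDI and names no treatment term. The effect on a treatment coefficient is therefore conditional on one being included.
- The regression sentence does not name technique. Its inclusion follows from reading the subgroup factors as those in the Subgroup analysis list. That is the natural reading, but the later promise of a separate analysis leaves room for a narrower one.
- A reader might fear that multiple imputation would assign a technique to collar patients. Nothing says so; a technique that does not apply is not a missing value.
- A reader might infer that the authors will claim equivalence from a non-significant test. No passage says that. The same stock sentence is used for baseline data, osteoporosis and sex.
- It would be too absolute to say that technique exists only in the surgical arm. Collar patients who cross over also receive a fusion. Their technique, too, is chosen after randomisation and not at random.
- The 18 evaluable patients and the splits are assumptions. With lower surgical mortality and an even split, the half-width falls below 3.5.

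None of this removes the core. The article fixes the factor, the comparison and the hypothesis, and says how technique is chosen; these do not fit together. That is more than detail left to a fuller document.

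**Conclusion.** The point holds as a moderate one about a secondary analysis. As listed, fusion technique is not a subgroup of the randomised comparison, and the Magerl against Goel-Harms contrast is confounded by the stated reasons for departing from the default. On the planning assumptions (25 operated, 29% mortality borrowed from non-surgical treatment, SD 3.5, splits from 15:3 to 9:9), the contrast has 32% to 51% power for the MCID and a half-width of 4.7 to 3.5 points, so a non-significant result could not support the stated hypothesis. If technique enters a two-arm NDI regression that also has a treatment term, that term no longer estimates the randomised contrast. The unadjusted between-arm comparison in Table 1 stands.

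**What to change.** 1. Take fusion technique out of both subgroup lists (Study outcome measures, and the later Subgroup analysis section).
2. State under Analysis of the primary outcome that technique is excluded from the two-arm NDI regression.
3. Replace the Table 1 row by a descriptive comparison among operated patients, giving an estimate and 95% CI. Label it as non-randomised and confounded by the reason for the choice, and drop the no-difference hypothesis. Say how crossovers and techniques outside the two named categories are counted.

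This changes wording only. It needs no extra data and does not touch the choice of technique. The cost is one exploratory p value.
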